### Objectives {7}

The primary aim of this study is to conduct an RCT to determine the effectiveness of remote, peer-delivered behavioural activation (BA) therapy, plus ongoing informal peer-support intervention to individuals with AD in reducing preterm birth. We hypothesize that our intervention will be associated with an increase in gestational age at delivery compared to the standard of care.

The secondary aims of this trial are to determine whether the peer-administered intervention will be effective for treating AD prior to delivery, with persistence to 6 and 12 months postpartum, improving anxiety symptoms compared to controls.

We hypothesize that participants in the intervention group will have:Significantly greater reduction in depression symptoms from T1 to T2, and significantly lower odds of depression at T2, T3 and T4 compared to controlsSignificantly greater reduction in anxiety symptoms from T1 to T2, and significantly lower odds of depression at T2, T3 and T4 compared to controls

We will also qualitatively explore the lived experiences of peer counsellors in delivering the trial intervention. We hypothesize that experiences providing the intervention to peers will be perceived as positive and that peer counsellors may identify perceived benefits to their own mental well-being.

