### Outcomes {12}

The primary outcome is gestational age at birth in days, measured using electronic health records, obtained for the P3 Cohort.

Secondary outcomes are:Change in symptoms of depression across T1 and T2 between the treatment and control groups, measured as overall score on the EPDS; and lower odds of scoring 13 or greater on the EPDS at T2, T3, and T4.Change in symptoms of anxiety across all timepoints (measured by the PROMIS – anxiety 7a-item short form self-report questionnaire [41])

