### Sample size {14}

This sample size of 246 participants (123 per group) is adequate to detect a minimally clinically significant change of 3 days in mean gestational age with 80% power at an α level of 5%. Based on a 2-sided *T*-test statistic and an α level of 5%, we will have 90% power to detect a minimally clinically significant difference of 25% in EPDS scores at intervention completion (T1), with a sample size of 214 participants [42]. We have inflated our estimated sample size by a factor of 15% (total *N*=246), to account for study attrition. A prior study demonstrated a reduction in EDPS scores up to 56% in a similar intervention during pregnancy [11]. A total of 60–75 peer counsellors will be recruited and trained to provide the intervention to between 1 and 3 participants through the course of the study. Additional peer counsellors will be recruited and trained as needed.

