## Statistical methods

### Statistical methods for primary and secondary outcomes {20a}

We anticipate that the block randomization will successfully eliminate confounding by covariates, but potential confounding variables will be measured on all questionnaires, and imbalance between intervention and control groups assessed prior to the final analysis. Any imbalance in confounding variables between the groups will be controlled for as appropriate, using cox proportional hazards or logistic regression modelling. Descriptive statistics will be calculated for all participant characteristics that have the potential to act as confounding variables on the primary association between the intervention and gestational age.

Time-to-event analysis will be used to assess change in our primary outcome of gestational age at delivery.

Logistic regression will be used to model the association between the intervention and categorical secondary outcome of depression (scoring 13 or greater on the EPDS), post-intervention, and 6 and 12 months postpartum. Secondary outcomes of difference in continuous scores on the EPDS (depression), PROMIS (anxiety), and parenting self-efficacy scales between intervention and control groups will be modelled using linear regression.

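### The 80% power is stated for a 3-day difference in means, but the primary analysis is time-to-event, and preterm birth, the stated aim, is not a listed outcome

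*Protocol article*

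**What the plan says.** Four sections of the protocol article bear on this.

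- **Objectives {7}.** The primary aim is the effectiveness of "ongoing informal peer-support intervention to individuals with AD in reducing preterm birth". The hypothesis that follows is on another scale: "our intervention will be associated with an increase in gestational age at delivery compared to the standard of care". The Abstract and Trial design {8} also speak of gestational age or gestational length.
- **Outcomes {12}.** "The primary outcome is gestational age at birth in days". The secondary outcomes are depression and anxiety. Preterm birth is not among them.
- **Sample size {14}.** The 246 participants (123 per group) are said to suffice for a "minimally clinically significant change of 3 days in mean gestational age" with 80% power at a 5% level. No SD, test, hazard ratio or event count is given. The t-test comes in the next sentence, which opens "Based on a 2-sided" and concerns EPDS scores (90% power, 214 participants).
- **Statistical methods {20a}.** "Time-to-event analysis will be used to assess change in our primary outcome of gestational age at delivery". Imbalances between groups are to be controlled "using cox proportional hazards or logistic regression modelling". Linear regression is assigned only to the questionnaire scores. No effect measure is named for the primary outcome.

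**The concern.** Three quantities are in play: a risk (preterm birth) in the aim, a mean in days in the sample size, and an event-time comparison in the analysis. Nothing connects them.

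Two consequences follow. First, the 80% is calculated for a difference in means, and a log-rank or Cox test can have quite different power for the same mean gain, depending on where in the distribution the gain arises. Second, every participant delivers, so every delivery is an event. If preterm birth is around 10–15% (an assumption; the article gives no rate), 85–90% of events are at term and term timing dominates the all-delivery test. The trial could miss a real fall in preterm birth, or report success on a shift among term births that prevents none. With no preterm-birth outcome listed, no other planned result would show the reader which had happened.

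**Working it through.** **1. The plan's own figure.** For a two-sided comparison of means, SD = δ / [(z₀.₉₇₅ + z₀.₈₀) × √(2/n)]. With δ = 3 days and n = 123 from Sample size {14}:

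SD = 3 / [(1.960 + 0.842) × √(2/123)] = 3 / 0.357 = 8.4 days.

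With 107 per arm it is 3 / [2.802 × √(2/107)] = 7.8 days. So 246 cannot be verified. It reproduces only if the SD was about 8.4 days. The total itself is the EPDS figure inflated: 214 × 1.15 = 246.1. At 123 per arm, power for 3 days over a range of assumed SDs is 84% (SD 8), 65% (SD 10), 50% (SD 12) and 39% (SD 14).

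**2. The same N on the hazard scale.** By Schoenfeld's formula with 1:1 allocation, HR = exp[−(z₀.₉₇₅ + z₀.₈₀) / √(events/4)]. If all 246 deliver, HR = exp(−2.802/√61.5) = 0.70; with 214 events, exp(−2.802/√53.5) = 0.68. The article gives neither a hazard ratio nor a conversion from 3 days to one.

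**3. What the planned type of test responds to.** Trials with 123 per arm and no censoring were simulated under two assumed distributions.

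- Set-up 1: preterm Normal(242, 14) capped at 258 days; term Normal(277, 7.5) floored at 259 days.
- Set-up 2: preterm 258 days minus an exponential with mean 16; term Normal(275, 8) restricted to 259–294 days. With 10% preterm the overall SD is about 13 days.

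A range in a cell reflects repeat runs.

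| Source of the gain | Set-up | Mean gain (days) | Log-rank, all deliveries | Comparison of means | Log-rank stopped at 37+0 |
|---|---|---|---|---|---|
| Preterm 12% to 3% | 1 | 3.3 | 13% | 55–56% | 80–82% |
| Preterm 10% to 2% | 1 | 2.9 | 11% | 49–50% | 80% |
| Preterm 10% to 0% | 2 | 3.3 | 14% | 72% | not run |
| Preterm 15% to 0% | 2 | 5.0 | 26% | 94% | not run |
| Uniform +3 days, 10% preterm | 1 | 3 | 74% | 41% | not run |
| Uniform +3 days, 10% preterm | 2 | 3 | 75% | 44% | not run |
| Uniform +3 days, 15% preterm | 1 | 3 | 68% | 34% | not run |
| Term births only, 10% preterm | 1 | about 3 | 80–84% | 40–41% | 5% |
| Term births only, 10% preterm | 2 | 3.1 | 89% | 44% | not run |
| Term births only, 15% preterm | 2 | 3.0 | 83% | 32% | not run |

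Under a plain normal shift of 3 days with SD 8.37, close to the implied value, the comparison of means has 80% power and the log-rank 73–74%.

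In set-up 2 at 10% preterm, the Cox hazard ratio is 0.90 when all preterm births are prevented, 0.72 for the uniform shift and 0.67 for the term-only shift, for mean gains of about 3 days in each case. Preterm deliveries carry about 6–11% of the log-rank information at 10% control preterm birth and about 9–17% at 15%.

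**4. Reading.** A gain of about 3 days gives log-rank power from 11% to 89%, depending on its source. The 80% calculated for a mean therefore cannot be carried over to the time-to-event test.

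**The case against.** The case for the protocol is substantial.

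- A reader might infer that the primary outcome was powered by a t-test. The text does not say so. The t-test belongs to the EPDS sentence, and for the 3 days a comparison of means is only implied. This objection stands.
- A reader might infer that the primary result will be a hazard ratio, giving neither days nor preterm risk. Cox is named only for adjustment, and no estimate is declared. With all deliveries observed, the restricted-mean difference up to the last delivery equals the mean difference in days, and the Kaplan-Meier estimate at 259 days gives preterm-birth risk. An unseen analysis plan may specify either. This stands too, but it does not link the stated power to the stated analysis.
- A reader might conclude that the time-to-event test is wrong and should give way to a comparison of means. The uniform-shift rows say otherwise: log-rank 68–75%, means 34–44%. A general lengthening of gestation is the stated hypothesis, and the log-rank test suits it better. The comparison of means also reaches only 49–56% in the set-up 1 preterm scenarios.
- The preterm scenarios are large. The Background cites an odds ratio of 1.56 for untreated depression. Removing that whole excess from an assumed 12% gives odds of (0.12/0.88)/1.56 = 0.087, or a risk of 8%. Under set-up 1 that is only about 1.5 days, with 7% power for the log-rank and 13% for the means. So preterm prevention of that size would not supply 3 days on its own. This weakens those rows as forecasts, but it does not change the conclusion that the all-delivery test is insensitive to preterm birth.
- Any account of why term timing might move, such as induction or planned caesarean practice, is outside the documents and is not relied on here.

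**Conclusion.** The concern holds in a limited form. Sample size {14} and Statistical methods {20a} are on different scales with nothing joining them, so the 80% is not shown to apply to the planned analysis. Objectives {7} names reducing preterm birth as the primary aim, and Outcomes {12} provides no outcome that measures it directly. Both are statements in the text, not details left for an analysis plan.

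The size depends on assumptions. For a gain of about 3 days with 123 per arm, all-delivery log-rank power is about 11–14% if the gain comes only from preterm births prevented (10% to 2%, 12% to 3% or 10% to 0%), about 75% for a uniform shift at 10% preterm, and about 80–89% for a term-only shift at that rate. The article supplies neither preterm rates nor a gestational-age distribution; other assumed rates widen the range. The ordering was the same in both set-ups.

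The documents do not support saying that the time-to-event analysis is invalid, or that it must be replaced.

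**What to change.** 1. Add preterm birth (before 37+0 weeks) as a named secondary outcome, reported as a risk difference with its 95% CI, as a time-to-event analysis censored at 259 days, or both.
2. Report the primary time-to-event result with a restricted-mean difference in days and its 95% CI, beside any hazard ratio, so that it can be set against the 3-day threshold.
3. Restate the power for the analysis actually planned, with the assumed SD or hazard ratio, and accept that the figure may fall below 80%.

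The cost is wording in the protocol and analysis plan, settled before outcome data are seen by arm. Data collection {18a} already obtains gestational age at delivery from linked records, so no new data are needed. The preterm-birth estimate will be imprecise: at an assumed 10% there are about 12 events in a control arm of 123 (0.10 × 123). Making a comparison of means the primary test instead would be a trade-off between effect patterns, and this point does not require it.

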### Trial design {8}

A trial within cohort design will be conducted [33]. A two-arm, single-blinded, parallel groups superiority design RCT with repeated measures will be used to evaluate the impact of remote (phone and/or online), peer paraprofessional-delivered BA and peer support on gestational length, compared to standard-of-care (SOC), among individuals with antenatal depression. Assessments will be conducted prior to 27 weeks’ gestation at trial intake (T1), within 1 week of inervention completion and prior to delivery (T2), 5–6 months postpartum (T3), and 11–12 months postpartum (T4). The current study will be conducted in adherence with the University of Calgary’s Conjoint Health Research Ethics Board (CHREB) regulations, and the 1964 Helsinki Declaration, and reported in accordance with CONSORT guidelines.

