#### Screening and enrollment

After informed consent is obtained for the P3 cohort, including consent to be contacted for nested trials, participants meeting the study definition of AD will be identified by research assistants using weekly data queries. For the purposes of this study, AD is defined as a score of 10 or greater on the Edinburgh Postnatal Depression Scale (EPDS), which has been validated to measure major depressive disorder against diagnostic interviews (sensitivity 87.7%; specificity 90.9%) in pregnant individuals [34, 35]. All participants with AD will be invited to join this nested trial. Participants will be contacted by trained research assistants, provided with study information, and invited to enrol in the current study.

Written informed consent will be obtained in addition to the P3 cohort consent. Research assistants will screen participants further for eligibility and included participants will be randomized to receive the intervention or standard of care (control). Randomization will be conducted using computer-generated, block-randomization into an intervention group and a control group (receiving standard of care).

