### Methods in analysis to handle protocol non-adherence and any statistical methods to handle missing data {20c}

Analysis will be completed in accordance with an intention-to-treat (ITT) model and will therefore include all participants, regardless of protocol adherence or missing data. A secondary sensitivity analysis will also be conducted including only those who completed the intervention with adherence to the treatment protocol.

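### Secondary EPDS and PROMIS analyses: the named regressions do not by themselves include participants with missing scores, and adjustment only on observed imbalance forgoes the precision of the T1 score

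*Protocol article*

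**What the plan says.** The relevant statements are spread over four sections of the protocol article.

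- **Trial design {8}** calls the trial a "superiority design RCT with repeated measures".
- **Outcomes {12}** defines the depression outcome as "Change in symptoms of depression across T1 and T2 between the treatment and control groups, measured as overall score on the EPDS", together with "lower odds of scoring 13 or greater on the EPDS at T2, T3, and T4". The anxiety outcome is "Change in symptoms of anxiety across all timepoints", which means T1 to T4.
- **Statistical methods {20a}** says that differences in continuous EPDS and PROMIS scores on these "scales between intervention and control groups will be modelled using linear regression", and that the EPDS cut of 13 is analysed by logistic regression at each follow-up. Adjustment is made for covariates found to be imbalanced, and the models named for that step are Cox and logistic. No visit term, within-person correlation or baseline covariate is mentioned.
- **Missing data {20c}** says that, because the analysis is intention-to-treat, it will "include all participants, regardless of protocol adherence or missing data". No method for doing so is named.

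**The concern.** Three things do not fit together.

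First, linear or logistic regression at a single visit uses only people who have the outcome at that visit. Intention-to-treat decides which arm a person is counted in; it does not supply a missing score. The inclusion statement therefore does not follow from the methods named.

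Second, Outcomes {12} speaks of change (two visits for EPDS, four for anxiety), while Statistical methods {20a} speaks of a difference in scores between arms. The text does not settle whether a change score or a follow-up score is analysed, or how one linear regression covers anxiety across all timepoints.

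Third, adjusting only when imbalance is observed makes the use of a strong prognostic variable depend on the data. T1 EPDS is known for every participant because it determines eligibility, and T1 PROMIS is collected. Adjusting for them improves precision whether or not the arms happen to differ.

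At stake are the precision of the secondary results and, if loss depends on mood differently in the two unblinded arms, some bias in them.

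**Working it through.** **Inputs from the protocol article.** Sample size {14}: two-sided t-test, 5% level, 90% power for a 25% EPDS difference with 214 participants, inflated by 15% to 246. (That section labels intervention completion T1; the trial design and timeline call it T2, and I read it as T2.) Sequence generation {16a}: 1:1 allocation. Retention {18b}: over 80% of the pilot sample kept for one year, so 20% is taken as an upper figure for loss.

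**The plan's own figures.** 214 × 1.15 = 246.1, which reproduces 246. The 214 cannot be reproduced because no EPDS mean or SD is given. Solved backwards with 107 per arm:

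d = (1.960 + 1.282) × √(2/107) = 0.443

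This d is implied by the plan, not stated in it.

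**Participants dropped at a visit by regression alone.**
- 15% loss: 0.15 × 246 = 36.9, about 37, leaving 209 (104.5 per arm).
- 20% loss: 0.20 × 246 = 49.2, about 49, leaving 197 (98.4 per arm).

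**Power.** Let r be the T1-T2 correlation (not in the documents; 0.3 to 0.5 assumed), with equal SDs at the two visits. Relative to the follow-up SD, the analysis SD is k = 1 for the T2 score alone, k = √(2(1−r)) for an unadjusted change score, and k = √(1−r²) with baseline adjustment. Then

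power ≈ Φ(d√(n/2)/k − 1.96)

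With n = 104.5, d√(n/2) = 0.443 × 7.228 = 3.203.

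| r | Change score | T2 score alone | Baseline-adjusted |
|---|---|---|---|
| 0.3 | 3.203/1.183 − 1.96 = 0.75 → 77% | 3.203 − 1.96 = 1.24 → 89% | 3.203/0.954 − 1.96 = 1.40 → 92% |
| 0.4 | 3.203/1.095 − 1.96 = 0.96 → 83% | 89% | 3.203/0.917 − 1.96 = 1.54 → 94% |
| 0.5 | 3.203/1 − 1.96 = 1.24 → 89% | 89% | 3.203/0.866 − 1.96 = 1.74 → 96% |

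At 20% loss (98.4 per arm) the same formula gives 75-87.5% for change, 87.5% for the T2 score and 90-95% adjusted. The variance of the change score relative to the adjusted analysis is 2(1−r)/(1−r²) = 2/(1+r), that is 1.54, 1.43 and 1.33 at r = 0.3, 0.4 and 0.5.

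**Bias from dropping incomplete participants.** An illustrative simulation used 246 participants, about 16% lost by T4, a true difference of 0.443, and loss depending on the previous score. Where that dependence ran in opposite directions in the two arms, a complete-case comparison of T4 scores gave 0.52, 0.57 and 0.61 at correlations of 0.3, 0.5 and 0.7. Adding baseline gave 0.47 to 0.49, and using all earlier visits gave 0.44. Where loss worked the same way in both arms, the complete-case error was at most about 0.02.

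**The case against.** The strongest reply is that much of this is silence. The article names a model family, and covariate lists, visit handling and imputation are commonly left to an analysis plan that is not shown. That reply disposes of several stronger readings.

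- *There is no baseline term.* A reader might infer this, but the article never says it. A T1-T2 change uses baseline by subtraction, and linear regression can carry a baseline covariate.
- *The planned power is lost.* Sample size {14} rests on a plain t-test with attrition budgeted, and an unadjusted T2 comparison keeps about 89%. A material shortfall needs both the unadjusted change-score reading and a correlation under 0.5.
- *The missing-data promise cannot be kept.* Multiple imputation before regression would keep it, and nothing rules that out.
- *The EPDS 13-or-more analysis is invalid because people enter below the cut.* Screening and enrollment says "AD is defined as a score of 10 or greater on the Edinburgh Postnatal Depression Scale" (the eligibility section also gives above 10), so some entrants already score under 13. But the stated aim is lower odds of being at or above 13, compared between randomised arms. That contrast is valid without baseline, and the article does not present it as recovery. The share of entrants below 13 is not documented.
- *Complete-case results will be biased.* Material bias in the simulation needed opposite dropout patterns by arm, which is an assumption.

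What the reply does not remove is in the text itself: inclusion is presented as following from intention-to-treat when the named methods do not deliver it, change and difference in scores are not aligned, and adjustment is triggered by imbalance.

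**Conclusion.** The point holds in this limited form. Used alone, the named regressions leave out about 37 (15%) to 49 (20%) of 246 participants at a visit, so the inclusion statement in Missing data {20c} needs a further method to be true. Prespecified adjustment for the T1 score gives the highest power at each correlation tried: 92-96%, against 89% for the T2 score alone and 77-89% for an unadjusted change score, with 209 analysed.

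These figures rest on a back-solved d of about 0.44, an assumed correlation of 0.3 to 0.5 and equal SDs at T1 and T2. If the entry cut narrows the T1 spread, the change score would break even with the T2 score at a correlation somewhat below 0.5.

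The change is worth making because it costs little. It concerns secondary outcomes only; gestational age at delivery is unaffected.

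**What to change.** 1. For EPDS and PROMIS, replace the imbalance-triggered rule with prespecified adjustment for the continuous T1 score of the same scale in every model. State how a missing T1 PROMIS is handled, since PROMIS is not an eligibility measure.
2. Analyse PROMIS, and EPDS with T2 as its main contrast, with a mixed model for repeated measures over T2 to T4: arm, visit, arm-by-visit, baseline and baseline-by-visit. Such a model still omits anyone with no post-baseline score. Alternatively, use baseline-adjusted regression after multiple imputation, which includes those participants too and so meets Missing data {20c} in full.
3. For EPDS 13 or more, include continuous baseline EPDS for precision and state that the odds ratio is then conditional on baseline.
4. Add a sensitivity analysis that assumes worse scores after dropout.
5. Use one wording for the outcome in Objectives {7}, Outcomes {12} and Statistical methods {20a}, and name the missing-data method in {20c}.

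The cost is protocol or analysis-plan wording and a little more analysis work. No new data are needed.
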